---

**Sponsor: *The Second Xiangya Hospital of Central South University***

## PROTOCOL SYNOPSIS

---

**A randomized controlled, open-label, multi-center study with 104-week saxagliptin or(and) vitamin D3 assessing protective effects on beta cell function in latent autoimmune diabetes in adults (LADA) treated with Metformin (and insulin)**

---

### Sub-Investigator (Sub-I):

Study site(s): 20-45 (China)

Number of subjects planned: 300

---

---

### Study period

|                                          |          |
|------------------------------------------|----------|
| Estimated date of first subject enrolled | Jan 2016 |
| Estimated date of last subject enrolled  | Apr 2017 |
| Estimated date of last subject completed | May 2019 |
| Estimated date of finalized study report | Dec 2019 |

---

### Study design

This is a multi-center, open-label, 1:1:1 randomized controlled trial, compromised of a 6-week run-in period and the 104-week treatment period.

---

Target population: LADA patients signed an informed consent ( the definition of LADA subjects please refer to the inclusion standards of the study) ; aged 18-70 years old; duration should be less than 4 years.

Randomize all subjects who meet all eligibility criteria and do not meet any of the exclusion criteria into three groups by a central dynamic random method: metformin (and insulin) , metformin (and insulin) + saxagliptin , metformin (and insulin) + saxagliptin + vitamin D3.

The main purpose of this study: evaluate whether saxagliptin (and vitamin D3) as add-on therapy to metformin (and insulin) can better protect islet beta cell function than metformin (and insulin).

Safety objective: Adverse events, serious adverse events, blood glucose, blood routine, serum creatinine, serum calcium and 25 (OH) D monitoring.

---

## Objectives

| Primary Objective:                                                                                                                                                                                                                                                                                                                                                                                                                                                                          | Primary Outcome:                                                                                                                                                                                                                                                                                                                                                                                                                                                                                                                                                                                                                                                              |
|---------------------------------------------------------------------------------------------------------------------------------------------------------------------------------------------------------------------------------------------------------------------------------------------------------------------------------------------------------------------------------------------------------------------------------------------------------------------------------------------|-------------------------------------------------------------------------------------------------------------------------------------------------------------------------------------------------------------------------------------------------------------------------------------------------------------------------------------------------------------------------------------------------------------------------------------------------------------------------------------------------------------------------------------------------------------------------------------------------------------------------------------------------------------------------------|
| 
 
1. To evaluate the efficacy of adjunctive saxagliptin to metformin (and insulin) on beta cell function in compared with metformin (and insulin) in LADA patients.
 
1. To evaluate the efficacy of adjunctive saxagliptin combined with vitamin D3 to metformin (and insulin) on <math>\beta</math>-cell function compared with metformin (and insulin) in LADA patients.
 
                                                          | 
Absolute changes from baseline in fasting C-peptide levels at week 104.
                                                                                                                                                                                                                                                                                                                                                                                                                                                                                                                                                                                                |
| Secondary Objective                                                                                                                                                                                                                                                                                                                                                                                                                                                                         | Secondary Outcome:                                                                                                                                                                                                                                                                                                                                                                                                                                                                                                                                                                                                                                                            |
| 
 
1. To evaluate the efficacy of adjunctive saxagliptin (and vitamin D3) to metformin (and insulin) on <math>\beta</math>-cell function in compared with metformin (and insulin) in LADA patients.
 
2. To evaluate the efficacy of adjunctive saxagliptin (and vitamin D3) to metformin (and insulin) on glycemic control /insulin-sparing/changes of autoantibody titer in compared with metformin (and insulin) in LADA patients.
 
 | 
 
1. Absolute changes from baseline in fasting C-peptide levels at week 26, 52 and 78.
 
2. Absolute changes from baseline in C-peptide at 60-min and 120-min (AUC) during a mixed-meal tolerance test at week 26, 52, 78 and 104.
 
3. The proportion of subjects with increased (decreased, unchanged) fasting or post-stimulus C-peptide level compared with baseline after 104 weeks of treatment.
 
4. The proportion of subjects with increased C-peptide pre-and post mixed-meal tolerance test (Delta C-peptide) after 104 weeks of treatment.
 
5. Changes of HbA1c levels from baseline
 
 |

|                                                                                                                                                                                                                                                                                                                                                                                                                                                                                  |                                                                                                                                                                                                                                                                                                                                                                                                                                     |
|----------------------------------------------------------------------------------------------------------------------------------------------------------------------------------------------------------------------------------------------------------------------------------------------------------------------------------------------------------------------------------------------------------------------------------------------------------------------------------|-------------------------------------------------------------------------------------------------------------------------------------------------------------------------------------------------------------------------------------------------------------------------------------------------------------------------------------------------------------------------------------------------------------------------------------|
|                                                                                                                                                                                                                                                                                                                                                                                                                                                                                  | 
at week 26, 52, 78 and 104.
 
6. The proportion of participants responding to hypoglycemic agents (defined as HbA1c<7%) after 104 weeks of treatment.
 
7. Changes of average daily insulin dose from baseline at week 26, 52, 78 and 104.
 
8. Changes of GADA titers from baseline at week 52 and 104.
 
9. Absolute changes of body weight and BMI Level from baseline at week 26, 52, 78 and 104.
 |
| Safety Objective:                                                                                                                                                                                                                                                                                                                                                                                                                                                         | Outcome Measure:                                                                                                                                                                                                                                                                                                                                                                                                             |
| To assess the safety of saxagliptin (and vitamin D3) in LADA patients treated with metformin (and insulin).                                                                                                                                                                                                                                                                                                                                                                      | 
AEs/SAEs, especially severe hypoglycaemia and potential hypercalcemia;
 
Vital signs;
 
Collection of clinical/chemistry parameters;
 
ECGs.
                                                                                                                                                                                                                                                                  |
| Exploratory Objective:                                                                                                                                                                                                                                                                                                                                                                                                                                                    | Exploratory outcomes:                                                                                                                                                                                                                                                                                                                                                                                                        |
| 
1. To evaluate the add-on effect of vitamin D3 on saxagliptin compared with saxagliptin monotherapy in LADA patients on the following factors:
 
 
a. Protection of <math>\beta</math>-cell function
 
b. Effect on glycaemic control
 
c. Effect on insulin-sparing
 
d. Effect on autoantibody titers
 
 
2. To investigate the relationship between genes and effects of saxagliptin and vitamin
 | 
1. Absolute changes from baseline in C-peptide at fasting, 60-min and 120-min (AUC) during a mixed-meal tolerance test at week 26, 52, 78 and 104.
 
2. The proportion of subjects with increased (decreased, unchanged) fasting or post-stimulus C-peptide level compared with baseline after 104 weeks of treatment.
                                                                                                  |

|                                                                  |                                                                                                                                                                                                                                                                                                                                                                                                                                                                                                                                                                                                                                                                                                                                    |
|------------------------------------------------------------------|------------------------------------------------------------------------------------------------------------------------------------------------------------------------------------------------------------------------------------------------------------------------------------------------------------------------------------------------------------------------------------------------------------------------------------------------------------------------------------------------------------------------------------------------------------------------------------------------------------------------------------------------------------------------------------------------------------------------------------|
| 
D3 in LADA patients treated with metformin (and insulin).
 | 
 
3. The proportion of subjects with increased C-peptide pre-and post mixed-meal tolerance test (Delta C-peptide) after 104 weeks of treatment.
 
4. Changes of HbA1c levels from baseline at week 26, 52, 78 and 104.
 
5. The proportion of subjects responding to hypoglycemic agents (defined as HbA1c<7%) after 104 weeks of treatment.
 
6. Changes of average daily insulin dose from baseline at week 26, 52, 78 and 104.
 
7. Changes of GADA titers from baseline at week 52 and 104.
 
8. HLA-DQ, DR and vitamin D receptor (VDR) gene polymorphism and immune repertoire polymorphism of patient before and after the treatment.
 
 |
|------------------------------------------------------------------|------------------------------------------------------------------------------------------------------------------------------------------------------------------------------------------------------------------------------------------------------------------------------------------------------------------------------------------------------------------------------------------------------------------------------------------------------------------------------------------------------------------------------------------------------------------------------------------------------------------------------------------------------------------------------------------------------------------------------------|

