## **Statistical methods**

All data are entered into SAS 9.3 software (SAS Institute Inc., Cary, NC, USA). The measurements will be calculated mean, standard deviation, median, quartile, minimum, and maximum. Categorical variables will describe as frequency and percentage. Changes from baseline in primary and secondary endpoints will be analyzed using a covariance pattern model, with treatment as classification variables and baseline value as a covariate. Point estimates and 95% confidence intervals (CIs) for the mean change within each treatment group, as well as for the differences in mean change between the two groups will be estimated. Differences in categorical variables will be analyzed using Pearson  $\chi^2$ , CMH  $\chi^2$  or Fisher probabilities. For primary outcomes,  $p < 0.025$  will be considered as significant. Other outcomes  $p < 0.05$  will be considered as significantly.

Adverse events (AEs) will be summarized. The incidence of adverse events will be summarized by body system organ class and preferred term. Analyses for safety and tolerability endpoints will be summarized using descriptive statistics for continuous variables or frequency counts and percentages for categorical variables. All conclusions will be based on final analysis rather than the interim analysis.

---

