|                                                                                                                                                    |                                                                                                                                                                                                                                                                                                                                                                                                                                                                                                                                                                                                                             |
|----------------------------------------------------------------------------------------------------------------------------------------------------|-----------------------------------------------------------------------------------------------------------------------------------------------------------------------------------------------------------------------------------------------------------------------------------------------------------------------------------------------------------------------------------------------------------------------------------------------------------------------------------------------------------------------------------------------------------------------------------------------------------------------------|
| 
(and insulin) on glycemic control /insulin-sparing/changes of autoantibody titer in compared with metformin (and insulin) in LADA patients.
 | 
mixed-meal tolerance test (Delta C-peptide) after 104 weeks of treatment.
 
 
5. Changes of HbA1c levels from baseline and at week 26, 52, 78 and 104
 
6. The proportion of participants responding to hypoglycemic agents (defined as HbA1c<7%) after 104 weeks of treatment
 
7. Changes of average daily insulin dose from baseline and at week 26, 52, 78 and 104
 
8. Changes of GADA titers from baseline and at week 52 and 104
 
9. Absolute changes of body weight and BMI level from baseline and at week 26, 52, 78 and 104
 
 |

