| 
1. To evaluate the add-on effect of vitamin D3 on saxagliptin compared with saxagliptin monotherapy in LADA patients on the following factors:
 
 
a. Protection of <math>\beta</math>-cell function
 
b. Effect on glycaemic control
 
c. Effect on insulin-sparing
 
d. Effect on autoantibody titers
 
 
2. To investigate the relationship between genes and effects of saxagliptin and vitamin D3 in LADA patients treated with metformin (and insulin).
 | 
1. Absolute changes from baseline in C-peptide at fasting, 60-min and 120-min (AUC) during a mixed-meal tolerance test at week 26, 52, 78 and 104.
 
2. The proportion of subjects with increased (decreased, unchanged) fasting or post-stimulus C-peptide level compared with baseline after 104 weeks of treatment.
 
3. The proportion of subjects with increased C-peptide pre-and post mixed-meal tolerance test (Delta C-peptide) after 104 weeks of treatment.
 
4. Changes of HbA1c levels from baseline at week 26, 52, 78 and 104.
 
5. The proportion of subjects responding to hypoglycemic agents (defined as HbA1c<7%) after 104 weeks of treatment.
 
6. Changes of average daily insulin dose from baseline at week 26, 52, 78 and 104.
 
7. Changes of GADA titers from baseline at week 52 and 104.
 
8. HLA-DQ, DR and vitamin D receptor (VDR) gene polymorphism and immune repertoire polymorphism of patient before and after the treatment.
 |

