## **4. STUDY SUBJECT**

### **4.1 Inclusion criteria/Exclusion criteria:**

#### **Inclusion criteria:**

- 1) Voluntarily joined with informed consent
- 2) The LADA patients to be included in this study are defined as:
  - (1) Meet the 1999 WHO Diagnostic Criteria for Diabetes Mellitus;
  - (2) Age at diagnosis  $\geq 18$  years old;
  - (3) GADA positive;
  - (4) Serum fasting C-peptide  $\geq 100\text{pmol/L}$  or 2-hour postprandial C-peptide  $\geq 200\text{pmol/L}$ .
- 3) Age between 18-70 years old
- 4) Duration of diabetes  $< 4$  years;
- 5) Outpatient or inpatient.

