#### **Exclusion criteria:**

- 1) Women who are pregnant, intending to become pregnant during the study period, or currently lactating females;
- 2) Gestational diabetes mellitus or other specific types of diabetes;
- 3) Allergy to saxagliptin, vitamin D3 and excipient;
- 4) Treated with medications including DDP-IV inhibitors, GLP-1 analogues, GLP-1 receptor agonists, and TZDs in the past 8 weeks prior to randomization;
- 5) Patients with hypercalcemia (exceeding the upper limit of the reference range )

- 6) Treatment with systemic corticosteroids therapy (oral or intravenous) consecutively for over 7 days in the past 6 months;
- 7) ALT or AST more than 3 times of the normal upper limit, TBIL more than 2 times of the normal upper limit;
- 8) Serum creatinine levels  $\geq 1.5$  mg/dL for males and  $\geq 1.4$ mg/dL for females or CrCl  $\leq 50$  mL/min;
- 9) Patients with malignant tumors;
- 10) Patients with mental disorders;
- 11) History of alcohol abuse or illegal drug abuse;
- 12) Serious systemic disease not suitable for the study by evaluation of the investigator.

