#### Second-line drug: Insulin, injected subcutaneously

- Daily dosage personalized

- The brand, dosage form, primary dosage, and frequency of insulin are decided by the investigator
- Advice towards the initiation of insulin: from the beginning of the screening stage, if the subject has a level of HbA1c  $\geq 7\%$ , the investigator can decide whether or not to initiate insulin treatment (on the basis of continuing metformin), in order to better control the patient's blood glucose level ( $\text{HbA1c} \leq 7\%$ )
- General advice towards the adjustment of insulin dosage:
  - The investigator should adjust the dosage and dosage form and decide whether or not to cease the use of insulin according to the patient's blood glucose level, physical condition, and the investigator's clinical experience;
  - First achieve the glycemic control at an average level and then adjust towards the ideal level, until the patient's blood glucose has reached standard or until the investigator thinks the patient's glucose level is best controlled
  - First avoid hypoglycemia and then control hyperglycemia.

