#### **9.4.2 Analysis of the secondary variable(s)**

The secondary endpoints including other parameters of  $\beta$ -cell function, for example C-peptide changes during MMTT. Glycaemic control parameters including HbA1c, FPG and PPG. Insulin-sparing effect is the difference of daily insulin dosage. One-way ANOVA will be used to examine the baseline data and the changes in AUC during MMTT, FPG, PPG, HbA1c and insulin dose between groups. The changes of secondary variables described above from the baseline within the same group and between groups will be analyzed with repeated measurement analysis of variance. The frequency counts

and percentages will be summarized on proportion of patients achieving  $\beta$ -cell function protection and glycaemic control.

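### Secondary outcome 6 labels HbA1c <7% at week 104 as response, although subjects already below 7% at entry count too, and the stated tests leave out their baseline HbA1c

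*Protocol*

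**What the plan says.** - **Outcome.** The Synopsis (Objectives, secondary outcome 6) lists "The proportion of participants responding to hypoglycemic agents", defined as HbA1c <7% after 104 weeks. Section 2.2 item 6 repeats it, and section 2.4 item 5 uses it for the exploratory comparison: "The proportion of subjects responding to hypoglycemic agents (defined as" HbA1c <7%. None of these places sets a condition on the starting value or requires a change from it.
- **Entry.** For glycaemia the inclusion criteria ask only that subjects "Meet the 1999 WHO Diagnostic Criteria for Diabetes Mellitus". The exclusion list, which ends with "Serious systemic disease not suitable for the study by evaluation of the investigator", has no HbA1c item.
- **Background treatment.** In section 5.2, for all arms, "the investigator can decide whether or not to initiate insulin treatment" when HbA1c is >=7%, with HbA1c <=7% as the aim. The Synopsis says the same.
- **Measurement.** Section 7.1 schedules HbA1c at V1, V5, V8, V14, V20 and V26. Baseline is therefore the Visit 1 value, and week 104 has one value. Section 6.4.1 has basic medication started or adjusted at Visit 1.
- **Analysis.** The Synopsis (Statistical methods) gives changes from baseline a model with the baseline value as covariate. For proportions it says "Differences in categorical variables will be analyzed using Pearson" chi-square, CMH chi-square or Fisher probabilities; section 9.4 lists the same tests. Section 9.4.2 adds that counts and "percentages will be summarized on proportion of patients achieving" beta-cell protection and glycaemic control.

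**The concern.** The word response tells a reader that treatment changed something. Under this definition a subject who enters at 6.5% and leaves at 6.9% has worsened and is still a responder. Improvement from background medication started at Visit 1, before randomization, also counts.

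Two things are at stake. First, a percentage described as responding to glucose-lowering drugs will be read as a drug effect when part of it is control that was already present. Second, subjects who are below 7% at the start and remain so in both arms add to both proportions without separating them. The arm difference shrinks, and a test that ignores baseline HbA1c does nothing to recover the lost precision.

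**Working it through.** **1. What the definition counts.** With no entry limit and no baseline condition, every subject falls into one of four cells. Baseline <7% and week 104 <7% is a responder; baseline >=7% and week 104 <7% is a responder; the other two are not. The first cell is target maintenance and the second is a change. The outcome adds them together. This follows from the text without any assumption.

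**2. How large the first cell is.** The protocol gives no HbA1c mean, SD, share below 7% or within-subject variability, so this can only be shown as a range. Assumed grid: baseline mean 6.5-9.0%, SD 1-2, mean true change 0 to -1.0, SD of change 0.5-1.0, within-subject SD 0.2-0.4. Share of week-104 responders already <7% at baseline:

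| Assumed baseline mean, SD | Assumed mean change | Share already <7% |
|---|---|---|
| 7.0, 1 | 0 | 72-83% |
| 8.0, 1 | -1.0 | 30-34% |
| 9.0, 1 | -1.0 | 9-15% |
| Whole grid | 0 to -1.0 | about 9-93% |

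**3. What it does to the arm difference.** Let p be the share already <7%. Assume that 85% of these stay <7% in both arms, and that 20% (control) and 40% (active) of the rest reach <7%. Then

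- control proportion = 0.85p + 0.20(1 - p)
- active proportion = 0.85p + 0.40(1 - p)
- difference = 0.20(1 - p)

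Take n = 80 per arm, which is the planned 100 less the protocol's 20% dropout: 100 x 0.80 = 80. Use two-sided alpha 0.05 and

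power = Phi{ [d - 1.96 sqrt(2 p̄(1 - p̄)/n)] / sqrt[(p1(1 - p1) + p2(1 - p2))/n] }.

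Example at p = 0.40: the proportions are 0.46 and 0.58, d = 0.12, p̄ = 0.52. The numerator is 0.12 - 1.96 x 0.0790 = -0.035, the denominator is 0.0784, and power is Phi(-0.44) = 33%.

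| p | Control | Active | Difference | Power |
|---|---|---|---|---|
| 0 | 20% | 40% | 20 points | 79% |
| 0.20 | 33% | 49% | 16 points | 54% |
| 0.40 | 46% | 58% | 12 points | 33% |
| 0.60 | 59% | 67% | 8 points | 18% |

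The example assumes that treatment does nothing for those already <7%. If treatment helps them stay there, the dilution is smaller.

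**4. What baseline adjustment recovers.** Simulated two-arm trials, 80 per arm, baseline and week-104 HbA1c with mean 7.5% and SD 1.2, a true 0.6-point difference, baseline to week-104 correlation 0.3-0.7, alpha 0.05:

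- Pearson chi-square: power about 68-70%
- logistic regression on treatment and baseline HbA1c: about 71-85%

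The gain is small at correlation 0.3 and largest at 0.7. All inputs except the 80 per arm are assumptions.

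**5. The boundary.** At exactly 7.0% a subject meets the stated aim (<=7%), is at the level where insulin may be considered (>=7%), and is a non-responder (<7% required).

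**The case against.** The definition is printed beside the label, so nobody is misled about what is counted. The parent objective is glycaemic control, and section 9.4.2 itself speaks of achieving it. Randomization balances subjects already <7%, so the comparison is not biased. In a trial about preserving beta-cell function, holding HbA1c below 7% for two years may be a real benefit. Baseline HbA1c is used elsewhere: as covariate for HbA1c change (secondary outcome 5) and among the factors in section 9.4.4. CMH is a stratified test, and section 9.1 promises an SAP.

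Most of this stands. It rules out a claim of bias, and it rules out demanding a minimum fall, which would score a subject held at 6.5% as a failure. It does not rescue the label. Nor does it supply the adjustment: CMH is one of three options, no strata are named, and the protocol has itself stated the tests, so they can fairly be improved.

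A reader might infer that most responders would be subjects already controlled at entry, or that measurement noise largely decides who is a responder. The documents support neither. The first depends on an unstated HbA1c distribution and on how far HbA1c falls; the table in step 2 of the working runs from a small minority to a large majority. As to noise, the share of responders whose true week-104 value was >=7% ran from about 1% to 37% on the same grid and never reached half.

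**Conclusion.** The point holds in a limited form. Secondary outcome 6 is target attainment under the name of response, and the tests stated for it make no use of a baseline value scheduled for everyone. The mislabelling follows from the text alone. The sizes do not: the dilution and power figures rest on assumed HbA1c distributions and effects, and the share of responders already <7% is not determined by the protocol. The expected consequence is a smaller arm difference and lower power, not bias between arms. The difference in wording at 7.0% is a small inconsistency to reconcile. The outcome is secondary and exploratory; the primary endpoint (fasting C-peptide) and the sample size are untouched.

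**What to change.** 1. In the Synopsis and sections 2.2 and 2.4, label the outcome *HbA1c <7% at week 104* and drop the reference to response.
2. In the Synopsis (Statistical methods) and sections 9.4.2 and 9.4.4, compare arms on this outcome by logistic regression with treatment and baseline (Visit 1) HbA1c, in place of an unadjusted test. Keep the observed proportion per arm beside it, since the odds ratio is conditional on baseline.
3. Report the proportion among subjects with baseline HbA1c >=7% as a supporting analysis.
4. Reconcile the <7% in the outcome with the >=7% and <=7% wording in the Synopsis and section 5.2, or state that they are meant to differ. This concerns consistency of wording only, not how insulin should be used.

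The cost is a change of text; no new data are needed. The supporting analysis has fewer subjects and is less precise, and its percentage will probably be lower than the overall one.
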